Recent investigations have yielded greater appreciation of the therapeutic potential of the placebo response. Increasingly more research has turned its focus to study ways in which to ethically harness that potential, and two main strategies have dominated these discussions. One stream of research employs principles of Pavlovian conditioning. By pairing placebo pills and clinical contextual cues (conditioned stimuli) with a physiologically active treatment (unconditioned stimuli), researchers have shown that medication dosages can be lowered without decreasing treatment efficacy. For example, Ader and colleagues demonstrated that placebos extend the effects of corticosteroids in psoriasis patients when given in accordance with a partial reinforcement paradigm. The frequency of disease relapse under this partial reinforcement paradigm was lower (26.7%) than in the control group (61.5%), outcomes which were clinically comparable to the reduction in symptoms induced by a full-dose regimen of corticosteroids (22.2%). Similarly, Perlis and colleagues applied a reinforced therapeutic schedule to medically manage chronic insomnia using 10 mg zolpidem pill with 50% active medication and 50% placebos for 12 weeks. The partial reinforcement group showed the same clinical benefit as the groups randomized to 10 mg or 5 mg or intermittent 10 mg nightly dosing. In a separate study, children with Attention Deficit Hyperactivity Disorder (ADHD) showed a therapeutic benefit when placebo pills were paired with a 50%-reduced dose of amphetamine. Thus, pairing a conditioned stimulus with amphetamines, corticosteroids, or zolpidem produced placebo conditioned responses that allowed individuals to be treated effectively with lower doses of the active medication. To date, this associative learning methodology has not been tested on methadone treatment or pain syndromes.

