## **2.0 PROJECT OVERVIEW**

**2.1 Brief project overview.** The broad goal of this proposal is to enhance treatment outcomes for OUD patients enrolled in a daily outpatient MT program. We will combine two well-known protocols for inducing placebo effects. Implementing principles of pharmacological conditioning, we will temporally pair placebo pills with the oral methadone solution that is provided to patients at the clinic, to ultimately use placebos as a conditioned stimulus. Additionally, we will apply an open-label paradigm: we will give the participants information concerning the placebo pill in an honest and transparent manner. This unique approach of combining two powerful protocols (pharmacological conditioning and open-label design) capitalizes on methods that have been robustly shown to enhance treatment outcomes in other patient populations. This proposal will allow us to conduct a proof-of-concept study to harness placebo effects with the ultimate scope of enhancing medication-based clinical treatment of Substance Use Disorder and minimizing methadone escalation.

**2.2 Specific Aims.** SA1: To compare the impact of pharmacologically conditioned open-label placebo to Treatment as Usual (TAU) on ultimate methadone dose achieved at 90 days. SA 2: To assess the effects of conditioned open-label placebo administration on 90-day MT outcomes and patient retention.

**2.3 Significance.** The findings obtained from these studies will provide crucial pilot data concerning the effectiveness of placebo interventions implemented in the context of substance use disorders, heretofore unexamined. Additionally, the data will contribute importantly to the growing literature on the translational applications of laboratory findings of manipulations involving the placebo effect in clinical practice by exploring a placebo effect in study participants with substance use disorder. To our knowledge, no data such as this exists in the drug addiction literature. If successful, this project will yield pilot data that will allow us to apply for larger funding opportunities using neuroimaging methodologies, with an aim to explore the mechanisms that underlie the placebo phenomenon in individuals with substance use disorders.

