#### **5.0 RESEARCH DESIGN AND METHODS**

**5.1 Overview of study design.** We propose to conduct a proof of principle investigation to test the impact of a conditioned, open-label placebo intervention on methadone treatment outcomes. One-hundred twenty new intakes into methadone treatment for OUD will be approached, consented, and randomly assigned to one of two conditions: conditioned open-label placebo (group C-OLP) plus methadone or methadone/Treatment as Usual (TAU). We will follow them

for three months for a total of five in-person meetings (baseline, two weeks, and 1-, 2- and 3- months post-baseline). For the first two weeks, we will implement principles of pharmacological conditioning whereby placebo pills are temporally paired with the oral methadone hydrochloride solution that is provided to patients at the clinic (conditioning phase). Having established an association and contextualized the placebo as part of the therapeutic experience, placebos are then used as a dose extension pill (week 3 up to three months). Additionally, we are applying an open-label paradigm, giving participants information concerning the placebo pill in an honest and transparent manner. Our primary outcome is methadone dose three months after (baseline) entry into treatment; secondary outcomes include several measures of treatment success including comprehensive urine toxicology screens, self-reported drug use, and treatment retention. We are also capitalizing on this unique patient access opportunity to measure several personality and environmental factors associated with OUD, as well as factors associated with placebo response. A complete schedule of all study-related procedures is presented in Table 1.

| Table 1. Assessment timeline                 |                     |                            |             |                        |             |             |
|----------------------------------------------|---------------------|----------------------------|-------------|------------------------|-------------|-------------|
|                                              |                     | Phase I
(Weeks 1 and 2) |             | Phase II
(Weeks 3+) |             |             |
|                                              |                     | Meeting (Day Number)       |             |                        |             |             |

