**5.7 Post-baseline meetings with study team.** Following the initial (baseline, Day 0) meeting, all participants will be asked to meet with a member of the study team at the following intervals: 14-, 28-, 56-, and 84-days following intake, periods of time that roughly correspond to 2 weeks, 1-, 2- and 3-months of treatment. Participants will be paid \$25 for each 30- to 45-minute study visit, for a total possible \$125. Because study participants are clients of the UMATC, they must come to the clinic daily for the first several months of their OUD treatment, facilitating follow-up with the study team (the research study team is co-located at the UMATC).

**5.8 Blinding.** At all stages of the study, methadone dose adjustments are conducted by an independent clinician blinded to treatment allocation and to when a participant is enrolled in the study. Additionally, because treatment allocation occurs only after Day 0 (baseline) assessments are complete, study team members are blind to treatment assignment for all of Day 0 procedures. Finally, data analysts are blind to treatment allocation.

**5.9 Urine toxicology screens.** Urine drug screening will occur *via* two methods: (1) a point-of-care Quik-tox screen (11 panel; LabCorp) conducted by clinic staff, results of which are reported immediately, conducted at baseline and then at monthly (random) intervals post-baseline; (2) and liquid chromatography–tandem mass spectrometry (LC-MS/MS) testing for a panel of more than 240 drugs, including new psychoactive substances, as well as other illicit and prescription

drugs. All testing is conducted by the Division of Forensic Toxicology, Armed Forces Medical Examiner System and coordinated by the University of Maryland, College Park Center for Substance Abuse Research (CESAR) staff. Urine is collected from participants during each of the five meeting times, and the Quik-tox screen is conducted only on samples from meeting one (baseline); the LC/MS/MS testing is conducted on all samples (baseline and 2 weeks, and 1-, 2- and 3-months post-baseline screening).

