## **6.0 OUTCOME ASSESSMENTS**

**6.1 Primary outcome.** Mean dose of methadone at 3 months (90 days) post-baseline (entry into treatment) will be recorded. These data are obtained from patient charts documenting daily records of methadone dose dispensed.

**6.2 Secondary outcome measures.** Secondary outcome measures include assessments of treatment retention, self-reported drug use, opioid withdrawal, craving, quality of life, and sleep. All measures will be obtained via facilitated self-report at all five time points, except for sleep, which will be measured only at baseline and one- and three-months post-baseline to maintain fidelity to the instrument's measure of "past-month" sleep.

**6.2.1 Treatment Retention.** Clinic attendance data will be obtained from participant Methasoft records. Three-month retention will be measured as a binomial variable (retained in treatment at the 90th day, yes/no). For descriptive purposes, retention also will be counted as the total number of days retained in treatment, starting at the participant's intake date, up to 3 months (90 days). The study team adopts the clinic's definition of discharge: 30 continuous days of treatment absence. For participants who are not retained in treatment at the 90th day, the last visit to the clinic prior to their discharge will be logged as the final day in treatment.

**6.2.2 Self-reported Drug Use.** Drug use is assessed via self-report of past-two-week use of four common substances: opiates (including heroin, fentanyl, and non-prescribed opioid use), cocaine, benzodiazepines, alcohol, and a fifth broad category of "other." The total number of days used (out of a total possible 14) will be recorded.

**6.2.3 Subjective Opiate Withdrawal Scale (SOWS).** The SOWS is a 16-item self-administered rank assessment of the severity of acute symptoms of opiate withdrawal, with anchor scores of 0 and 4 corresponding respectively to "not at all" and "extremely," for a possible total score of 64.

**6.2.4 Objective Opiate Withdrawal Scale (OOWS).** The OOWS is a 13-item experimenter-administered assessment of objective symptoms of opiate withdrawal (e.g., yawning, perspiration); symptom presence is scored a “1” for a possible total score of 13.

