### **7.3 Data analysis plan for secondary outcomes.**

**7.3.1 Treatment retention.** Chi-square analysis will be used to test group differences for the secondary outcome of treatment retention (continuous, up to 90 days).

**7.3.2 All other secondary outcomes.** Participants' self-reported days of drug use in the last 14 days was logged at each of the 5 total possible study visits. This information will be analyzed separately for opiates, cocaine, benzodiazepine, alcohol, and "other" drug use. For each variable, a mixed-effects longitudinal regression model will be fit to estimate and compare the mean number of days of reported drug use at each study visit by study group. The model follows:

$$\begin{aligned} \text{Expected}(\text{Numdays}_{ij}) = & \beta_0(\text{Baseline}_{ij}) + b_{0i} + \beta_{C\text{-OLP}2}(\text{C-OLP}2_{ij}) + \beta_{C\text{-OLP}3}(\text{C-OLP}3_{ij}) + \\ & \beta_{C\text{-OLP}4}(\text{C-OLP}4_{ij}) + \beta_{C\text{-OLP}5}(\text{C-OLP}5_{ij}) + \beta_{C\text{-OLP}2}(\text{TAU}2_{ij}) + \beta_{C\text{-OLP}3}(\text{TAU}3_{ij}) + \beta_{C\text{-OLP}4}(\text{TAU}4_{ij}) + \beta_{C\text{-OLP}5}(\text{TAU}5_{ij}) \end{aligned}$$

where

$\text{Numdays}_{ij}$  = Number of days of drug use for the  $i$ th person at the  $j$ th time point

$b_{0i}$  = Mean-0 normal random effect for subject  $i$ .

511 Baselineij = 1 if j=1, 0 otherwise.

512 C-OLP2ij = 1 if the patient is in the C-OLP group and time=2, 0 otherwise

513 TAU2ij = 1 if the patient is in the TAU group and time=2, 0 otherwise

514 and

515 remaining terms defined analogously.

516 By including a random effect for participant, the means are implicitly adjusted to account for  
517 differential dropout based on prior values of these variables. This model is fit using SAS proc  
518 mixed. At each time point, the hypothesis will be tested that the mean of the two groups differed.  
519 If we find that all the time-point means differed in the same direction, we would also perform a  
520 global (4 degrees of freedom) test of a difference between the groups at all four follow-up time  
521 points. For each drug analysis we will only include participants who used the drug at least once  
522 in the two weeks prior to baseline. All exploratory outcomes (OOWS, SOWS, Craving and  
523 WHO-QOL) will be analyzed in the same way as number of days of drug use, using the mixed  
524 effects longitudinal regression model.

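### The self-reported drug-use models keep only baseline users of each drug, so new non-opiate use is collected but enters no between-arm analysis that the protocol specifies

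*Protocol*

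**What the plan says.** Section 6.2.2 defines the outcome: "Drug use is assessed via self-report of past-two-week use of four common substances" plus a fifth, broad category, recorded as days used out of 14. Table 1 schedules this assessment for all participants at all five meetings.

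Section 7.3.2 then says: "This information will be analyzed separately for opiates, cocaine, benzodiazepine, alcohol, and 'other' drug use". Each variable gets a longitudinal mixed model with group-by-visit means and a random participant effect. The analysis set is fixed by a further rule: "For each drug analysis we will only include participants who used the drug at least once" in the two weeks before baseline. The section gives no other analysis of drug use. It states no such restriction for withdrawal, craving or quality of life, and section 7.3.1 states none for retention.

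The overview in section 2.1 gives the purpose as better treatment outcomes together with "minimizing methadone escalation". The second specific aim in section 2.2 is: "To assess the effects of conditioned open-label placebo administration on 90-day MT outcomes and patient retention".

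Section 5.1 adds that "secondary outcomes include several measures of treatment success including comprehensive urine toxicology screens, self-reported drug use, and treatment retention". Section 5.9 has mass-spectrometry testing run on the urine from every meeting. Urine toxicology is not in the list of secondary outcomes in section 6.2, and section 7 specifies no analysis for it.

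**The concern.** The trial tests whether an open-label placebo can hold methadone dose down. The Background motivates this with work on other drugs in which "researchers have shown that medication dosages can be lowered without decreasing treatment efficacy". A lower dose is good news only if patients do as well on it, and drug use is one of the measures by which that would be judged.

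Restricting each model to baseline users suits one question: how far does existing use fall? It does not address a second: do people who were not using a drug take it up? Someone with no benzodiazepine use in the fortnight before intake who then uses daily is absent from the benzodiazepine model. The rule is stated outright and applies to all five substances, so it is not a detail left open for a later document.

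At stake is what can be concluded. If dose were lower in the C-OLP arm and the five models showed no adverse difference, a reader could take that as evidence against substitution. The models could not show uptake of a new non-opiate drug, whichever arm it occurred in.

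**Working it through.** **The plan's own figure.** Section 7.1 gives the only power statement: 60 per group, 70% versus 44% or at most 26/60, Fisher exact test, two-sided 0.05, power 0.80. Exact enumeration gives 0.784 at 44% and 0.806 at 26/60, so it reproduces. It concerns dose escalation and has no bearing on drug use.

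**Inputs.** From the protocol: 60 per arm (section 7.1), five substances, and the inclusion rule (section 7.3.2). Baseline prevalence *q* of each drug and the rate of new use are not given, so the values below are assumptions that show a range. Section 5.5 also mentions a 60:40 allocation, which would change the per-arm counts but not the mechanism.

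**Step 1: who is left out.** Analysed per arm = 60*q*; left out = 60 − 60*q*. The difference detectable at one visit with 80% power, in SD units, is (1.96 + 0.84) × √(2/n), with n analysed per arm.

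| Assumed *q* | Analysed per arm | Left out per arm | Detectable difference (SD) |
|---|---|---|---|
| 95% | 57 | 3 | 0.52 |
| 60% | 36 | 24 | 0.66 |
| 40% | 24 | 36 | 0.81 |
| 25% | 15 | 45 | 1.02 |
| 15% | 9 | 51 | 1.32 |

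The first row is meant to resemble opiates and the others the remaining categories.

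**Step 2: new use that is not counted.** At *q* = 25% there are 45 baseline non-users per arm. If 5% in TAU and 20% in C-OLP took up the drug, that is 45 × 0.05 = 2.25 and 45 × 0.20 = 9. The restricted model counts none of these. That zero follows from the inclusion rule and does not depend on the assumed rates.

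**Step 3: what an added analysis could show.**
- In the same example, if each new user reported 4 days of use, the all-participant mean would differ by (0.20 − 0.05) × 4 × 45/60 = 0.45 days out of 14. Fisher power on the counts would be 0.48.
- With a smaller contrast, *q* = 20% leaves 48 non-users per arm. At 12% versus 4%, 48 × 0.12 = 5.8 and 48 × 0.04 = 1.9, about 6 versus 2. The two-sided Fisher p for 6/48 versus 2/48 is 0.27, and power at those rates is about 0.15.

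So an added analysis would make new use visible by arm, but would often not establish a difference.

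**Step 4: bias.** Use before baseline is fixed before randomisation. Selecting on it leaves the arms comparable within the subset. The rule narrows the population described and does not bias the contrast.

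**The case against.** The strongest reply is that this is a choice of target population and a defensible one. A days-of-use model with normal random effects behaves poorly with many zeros, and including people who never used a drug dilutes any reduction. This stands. It is a reason to keep the baseline-user model, though not a reason to have no analysis of the others.

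Three stronger readings are tempting, and the protocol supports none of them.

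- A reader might infer that new use would be invisible. It would not. Days of use are asked of everyone at every meeting, a post-baseline drug history is taken at Days 14, 28, 56 and 84 (Table 1, section 6.3.2), and mass spectrometry is run on all study urine samples. What is missing is a specified comparison. An analysis plan not at hand might cover the urine results, but it would still face the explicit restriction on self-report.
- A reader might infer that the second specific aim fails. It covers treatment outcomes and retention and does not name substitution. The retention, withdrawal, craving and quality-of-life analyses carry no such restriction. Opiate use, where an inadequate dose would most directly appear, is nearly intact: section 5.3 enrols new methadone initiates with moderate-to-severe disorder and excludes transfers. Increased use of any drug by its baseline users also stays in the models.
- A reader might infer that a safety signal is hidden. Clinic urine screening is monthly, adverse events are assessed at each visit (section 8.2), and a monitoring board reviews the study (section 8.3). Nor does the protocol say that it would report a lower dose as free of worsening drug use.

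It is also fair to object that the prevalences and uptake rates are not the trial's own. They illustrate scale only.

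**Conclusion.** The point holds in a limited form. As written, no specified between-arm analysis includes new use among baseline non-users, so the drug-use models cannot support a claim that a lower methadone dose came without new non-opiate use. This follows from the inclusion rule alone.

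Its size depends on unknown prevalences: about 3 of 60 per arm left out at 95%, and 24 to 51 of 60 at 60% down to 15%. That opiates are little affected is an expectation from the eligibility criteria, since the protocol gives no figure. New use here means use after none in the two weeks before baseline, so it includes resumption by earlier users.

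This is an inexpensive improvement that widens what the trial can conclude. It is not an error that invalidates the planned comparison.

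**What to change.** In section 7.3.2:

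1. Keep the baseline-user model and state that it addresses change in existing use.
2. For each substance, add an analysis of all randomised participants, either any use or days used by visit, with baseline use (yes/no) as a factor.
3. Report by arm the number of baseline non-users with any use at Days 14, 28, 56 or 84, with the number assessed, and label these counts descriptive.
4. State that any difference in methadone dose will be interpreted alongside these results.

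No new data are needed, because self-reported use is already collected from everyone at all five meetings. The cost is a few sentences and a few tables. The added analyses will contain many zeros, will be less sensitive to reductions than the baseline-user model, and will have low power for differences in new use. Absence of a significant difference should therefore not be read as evidence of no new use.

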## **8.2 Collection and reporting of non-serious adverse events and serious adverse events**

**8.2.1 Adverse events:** Adverse events associated with placebo pill treatment emergent events will be assessed systematically at each visit. This will provide detailed information on the potential for adverse events occasioned by placebo treatment. All adverse events will be discussed and reported to the IRB. A serious and unexpected adverse experience during the course of the research project, regardless of cause, will be reported to the IRB within 24 hours. UMB policy mandates that initial notification of the event can be made by telephone but must be followed promptly (within 7 days) with a written report, using a "Report of Adverse Experience" form and a copy of the signed consent document. A copy of the "Report of Adverse Experience" will be sent to the UMB Human Research Protections Office through a formal IRB procedure.

**8.2.2 Management of serious adverse events or other study risks:** Adverse events will be evaluated at each clinic visit. All non-serious and serious adverse events will be discussed with

the PI as well as with study physicians daily and during weekly case management meetings. Serious adverse events will be reported to the IRB and NIDA according to the reporting guidelines described above.

**8.2.3 Trial stopping rules:** Throughout the trial, if the participation of a subject is deemed unsafe, he or she will be discontinued from the trial. Examples of unsafe conditions include serious adverse events that are related to the use of the placebo pill, or psychological stress due to the assessments used in the course of the research. Measures have been taken to minimize any risk to our participants. Subjects are free to discontinue from the study and to refuse to participate in any of the procedures.

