**9.6.3.3 Risks associated with psychological questionnaires** (highly unlikely, not very serious): The questionnaires are short, but there is a chance that a participant could become emotionally upset or tired while taking them. Participants will be told that they do not have to answer any questions that make them feel emotionally upset. To minimize tiredness, participants will be given breaks during the study procedure if needed and will be told that they can cease their participation at any time without needing to provide an explanation. However, we do not anticipate that this will be a major risk: study interviews and questionnaires and the behavioral intervention have been used in prior research and elicit minimal distress or discomfort. They are not harmful or unpleasant. Some participants may experience some embarrassment discussing personal information about their drug use history or when participating in the study interviews. The major costs to participants involve the time required to complete the assessments and to participate in the study procedures. Other possible psychological risks can include distress and heightened sensitivity, which can occur as part of the behavioral treatments, clinical interviews, or completing self-reported ratings and questionnaires.

**9.6.3.4 Risks associated with the time-limited nature of the study** (somewhat likely, not serious): Individuals who are assigned to the C-OLP (intervention) arm will have an opportunity to elect to continue receiving placebo pills beyond the initial three-months of their participation in the study, whereupon they would receive up to one additional week's worth of the placebo pills (14 pills total), and told to take them PRN, if they feel a strong urge to do so. Participants who find that the placebo pills are helpful to their treatment may experience distress when their participation in the study ceases, and they are no longer able to receive placebo pills. To minimize this risk, psychological counseling will be available to participants at the end of their participation in the trial.

**9.6.3.5 Unforeseen adverse reactions to the placebo pills** (highly unlikely, moderately serious): The placebo pills are formulated as physiologically inert pills. We do not expect the

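### Section 8.2.1 ties systematic adverse event assessment to the placebo pill, section 8.2.2 covers all events, and Table 1 schedules no assessment in either arm

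*Protocol*

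**What the plan says.** Protocol section 8.2.1 describes the only adverse event assessment that the document calls systematic: "Adverse events associated with placebo pill treatment emergent events will be assessed systematically at each visit". The next sentence gives the purpose: "This will provide detailed information on the potential for adverse events occasioned by placebo treatment". The same section then says "All adverse events will be discussed and reported to the IRB", and adds an expedited rule: "A serious and unexpected adverse experience during the course of the research project, regardless of cause, will be reported to the IRB within 24 hours".

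Section 8.2.2 is broader. It says "Adverse events will be evaluated at each clinic visit", and "All non-serious and serious adverse events will be discussed with" the principal investigator and the study physicians. It sets no restriction by arm or by cause.

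Table 1, which section 5.1 presents as the full schedule of study procedures, has no line for adverse events.

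**The concern.** The two sections set different scopes for the same activity, and nothing says which one staff should follow. Under 8.2.1 taken alone, cause is judged when the event is collected. TAU participants take no pill (section 5.6), so the rule gives staff nothing to ask them. Adverse event counts by arm could then reflect how events were sought and not how often they occurred.

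This matters more here than it would for a drug with its own toxicity. Section 9.6.3.5 states "The placebo pills are formulated as physiologically inert pills", so pill reactions are not the main thing to watch. Section 2.1 gives the aim as "enhancing medication-based clinical treatment of Substance Use Disorder and minimizing methadone escalation". If the trial achieves that aim, the safety question is whether lower methadone doses come with other harms. Such events are unlikely to be put down to an inert pill.

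**Working it through.** No figure in the protocol bears on this point, so the check sets the provisions side by side.

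| Provision | Arms | Limited by cause? | What it can record |
|---|---|---|---|
| 8.2.1, per-visit assessment | In effect C-OLP only | Yes, at collection | Events linked to the pill |
| 8.2.1, reporting to the IRB | Both | No | Only what has already been collected |
| 8.2.1, 24-hour rule | Both | No | Events both serious and unexpected |
| 8.2.2, evaluation and discussion | Both | No | All events, with no method of asking stated |
| Table 1: SOWS, OOWS, craving, past-two-week drug use, constipation score (five visits) | Both | No | Withdrawal, craving, use, constipation |
| Table 1 and 6.3.7: methadone side effects checklist (days 14, 28, 56, 84; no baseline) | Both | Methadone side effects | Severity of 38 symptoms |
| 5.9: LC-MS/MS urine testing (five visits) | Both | No | Substances detected |
| 6.2.1 and 9.2: clinic records | Both | No | Attendance, retention or discharge, clinic urine screens |
| 8.3.3: DSMB review | Both | No | Adverse events, serious adverse events, retention, reasons for dropout where appropriate |

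**Step 1: scope of 8.2.1.** The first sentence is garbled and could be a loose reference to treatment-emergent events in general. The purpose sentence after it speaks only of events caused by the placebo, which supports the pill-only reading.

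**Step 2: who judges cause.** Allocation is revealed on Day 0 (section 5.5). Section 5.8 keeps the dose-adjusting clinician and the data analysts blind, but blinds the study team only for Day 0 procedures. Study staff asking about events at later visits may know the arm.

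**Step 3: whether 8.2.2 settles it.** It is wide enough to cover both arms and all causes. But it gives no method of asking, and its visit could be the daily dosing attendance or one of the five study meetings. It does not say that it overrides 8.2.1, and Table 1 does not help.

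**Step 4: what is measured elsewhere.** Only the starred items in Table 1 are confined to C-OLP: the order form, placebo compliance and the post-baseline pill information sheets. Withdrawal, craving, drug use, retention and methadone side effects are therefore measured in both arms. None of these instruments is described as recording overdose, hospital admission or death, and the record extraction in section 9.2 does not list them.

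**Step 5: direction and size.** If staff follow 8.2.2 alike in both arms, there is no differential ascertainment. If they follow 8.2.1 and attribute events to the pill freely, C-OLP shows a spurious excess. If they follow 8.2.1 and treat the pill as inert, few events are recorded in either arm and a real difference could be missed. The protocol states no adverse event rate, so no number can be attached to any of these.

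**The case against.** The strongest reply is that 8.2.1 does not say that only pill-related events are collected. The two sections can be read together: all events are evaluated at each visit, and pill-related ones receive extra, systematic attention. On that reading TAU is covered, and 8.2.1 itself sends all adverse events to the IRB. Most of the harms that might accompany a lower dose are already scheduled outcomes in both arms. The protocol sets no limit on methadone, and doses are adjusted by a clinician blind to allocation and enrolment. The wording of questions and the tabulation of events may sit in the case report form, the planned SOP manual or an SAP that is not at hand.

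Much of this stands. The combined reading is possible, and it bounds the problem. It is not stated, however, and it leaves pill-related events assessed more closely than all others, which is still an asymmetry between the arms. An SAP can decide how events are tabulated, but it cannot recover events that were never elicited. The IRB reporting sentence likewise passes on only what has been recorded.

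**Conclusion.** The point holds as a conflict between two collection rules, with a possible bias in adverse event counts by arm. It should be corrected, but it does not touch the primary analysis of methadone dose. The size of the bias is unknown. The conclusion assumes that staff might apply 8.2.1 as worded and that no document outside the protocol already imposes one rule for both arms.

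A reader might infer two stronger things, and the protocol supports neither:

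- **That TAU would have no safety record.** Section 8.2.2 is not limited by arm, and the withdrawal, craving, drug use, retention and side effect measures apply to both groups.
- **That the DSMB could not weigh risk against benefit.** Section 8.3.3 gives it adverse events, serious adverse events, retention and dropout reasons, and outcome data if available.

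What remains is that the adverse event part of that evidence may not be collected alike in the two arms, and that overdose, hospital admission and death have no dedicated collection in either.

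**What to change.** Reconcile 8.2.1 with 8.2.2 in one rule:

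- At every post-baseline study visit (days 14, 28, 56 and 84), ask every participant the same cause-neutral question about all adverse events since the last visit.
- Record attribution to the pill, methadone or another cause afterwards, as a separate field.
- Add the assessment as an unstarred row in Table 1.
- Record overdose, hospital admission and death explicitly in both arms. Someone who has died or is in hospital cannot answer at a visit, so name a second source; if that is the clinic record, extend the list in section 9.2 to match.
- Tabulate adverse events by randomised arm.

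The cost is protocol and case report form wording, plus matching consent or authorisation wording if section 9.2 is extended. Visit time rises by about one to two minutes, or 4 × 1 to 4 × 2 = 4 to 8 minutes per participant over the study, at visits that both arms already attend. The real downside is more non-serious events to record and report, mainly from TAU.
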